**Methods:**

The REALYSA (“REal world dAta in LYmphoma and Survival in Adults”) study is a real-life multicentric cohort set up in French areas covered by population-based cancer registries to study the prognostic value of epidemiological, clinical and biological factors with a prospective 9-year follow-up. We aim to include 6000 patients over 4 to 5 years. Adult patients without lymphoma history and newly diagnosed with one of the following 7 lymphoma subtypes (diffuse large B-cell, follicular, marginal zone, mantle cell, Burkitt, Hodgkin, mature T-cell) are invited to participate during a medical consultation with their hematologist. Exclusion criteria are: having already received anti-lymphoma treatment (except pre-phase) and having a documented HIV infection. Patients are treated according to the standard practice in their center. Clinical data, including treatment received, are extracted from patients’ medical records. Patients’ risk factors exposures and other epidemiological data are obtained at baseline by filling out a questionnaire during an interview led by a clinical research assistant. Biological samples are collected at baseline and during treatment. A virtual tumor biobank is constituted for baseline tumor samples. Follow-up data, both clinical and epidemiological, are collected every 6 months in the first 3 years and every year thereafter.

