### Recruiting centers

The recruiting centers meet at least one of these two criteria (see Fig. 2): 1) being an active center of the Lymphoma Study Association (LYSA) network with a good potential of patient recruitment and robust research facilities; 2) being located in a geographical area (i.e. French *département*) covered by a population-based cancer registry (PBCR). LYSA is the French cooperative group on lymphoma, federating researchers and medical practitioners from more than 80 healthcare centers throughout the country, in order to promote clinical research on lymphoma as well as improve prevention, management and treatment of lymphoma patients. Regarding registries, the French cancer surveillance system is an opt-out system, so any patient with a confirmed diagnosis of cancer and living in areas covered by a population-based cancer registry is automatically registered without specific patient consent, thus ensuring the exhaustivity of cancer incidence registration in these areas. PBCR are organized in a collaborative network named FRANCIM [31]. The main objectives of this network are to coordinate the 14 general cancer registries and 11 specialized cancer registries, to harmonize patient’s registration and data quality, to provide epidemiological indicators (incidence, survival, prevalence) and to coordinate epidemiological surveillance and research on cancer. PBCR will be useful to assess and eventually improve representativeness of the REALYSA cohort. Thirty-five French hospitals/clinics are currently participating to the study, including 18 (51%) large University Hospitals, 10 (29%) smaller general hospitals, 4 (11%) cancer centers and 3 (9%) private healthcare facilities. Other centers may open during the recruitment phase, if deemed necessary.

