### Statistical analysis

#### Sample size calculation

No sample size calculation is strictly required for cohort studies but was needed for planning and funding perspectives. We have therefore used a pragmatic approach, based on one of the objectives of the study, which is to be able to detect an association between the exposure of interest and the clinical outcome of interest (e.g. response to treatment, progression-free survival, overall survival – see section on clinical outcomes) for a given lymphoma subtype. First, using lymphoma incidence rates [3, 39] in the geographical study zone, we estimated the number of new lymphoma cases that could be recruited in REALYSA over a 4-year recruitment period. Second, we calculated the hazards ratio (HR) that this study would be able to detect as a function of the number of events, which can be then back transformed to a number of patients of a given lymphoma subtype.

Firstly, based on the initially planned recruiting centers, we would expect 2796 new lymphoma cases yearly, so a total of 11,183 new cases during the 4 years of inclusion (unpublished data coming from an extraction of registry data). Considering a participation rate of 70% and an improving dynamic recruitment rate (40% during the 1st year, 75% the 2nd year, and 100% on the last 2 years), the number of cases that could be recruited in REALYSA is around 6000 patients (exactly 6165 patients, distributed as follows: 911 patients with HL, 2123 patients with DLBCL, 1294 patients with follicular lymphoma (FL), 344 patients with mantle cell lymphoma (MCL), 88 patients with Burkitt lymphoma, 958 patients with MZL and 447 patients with NHL-T).

Secondly, we calculated the detectable HR assuming a binary exposure of interest (say “present” vs “absent”). We relied on the proportional hazard model to describe the association between the exposure and the mortality hazard, with a 2-sided test at α = 0.05 (type 1 error rate) and a desired 80% power (i.e. 1 minus the type 2 error rate). With a pre-specified value for the prevalence of the exposure in our sample, we can obtain the detectable HR as a function of the number of events [40]. In order to get an absolute measure of the difference between groups (as opposed to the HR, which is a relative measure), one could use the link between HR and survival. This would allow to express the difference between the survival of the exposed, *S*_1_(*t*), and the unexposed *S*_0_(*t*) as: *S*_1_(*t*) = *S*_0_(*t*)^*HR*^.

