We investigated scenarii with 3 levels of prevalence for the exposure: 10, 20 and 30%. The results are shown in Fig. 3 with the detectable HR according to the number of events. We would need to observe 530 events to be able to detect a HR of 1.5 with a type I error rate of 0.05, a power of 0.8 and an exposure prevalence of 10%. Therefore, if we assume that the proportion of events among the cases is approximately 30% (as observed for example for DLBCL for 1-year survival in France [7], and assuming no lost-to-follow up), then we need to observe 1767 patients with DLBCL (530/0.3). This HR of 1.5 in the context of DLBCL would then correspond to a 1-year survival of 70% in the unexposed group vs 59% in the exposed group. Despite the fact that this approach for sample size calculation relies on many assumptions, it has the advantage of being general and versatile to our different settings (i.e. according to lymphoma subtype and clinical outome of interest).

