#### Generalities on the statistical methods for basic description of the association between the variables and time-to-event outcomes

Continuous variables will be summarized in tables displaying sample size, mean, standard deviation, median, and range; quartiles will also be presented when considered relevant. Categorical variables will be described in counts and percentages, including a specific category for missing data. Time to events will be described using Kaplan-Meier method, and survival probabilities (with the corresponding curves) will be provided with their 95% Confidence Interval (CI). For (semi-) competing risks setting (i.e. dealing with multiple event types), cumulative incidence functions will be our measure of interest.

Association between a categorical baseline prognostic factor and the time to event will be assessed by a two-sided log-rank test and quantified with a hazard ratio (HR) with 95% CI as estimated from a Cox model including only this variable as predictor. The continuous baseline prognostic factors will be categorized using the quantiles of their observed distribution and we will apply the same strategy as the categorical prognostic factors. Additionally, for the continuous factors, we will use their original version in a survival model (e.g. Cox or flexible parametric model) to estimate the (eventually time-dependent) HR associated with a 1-unit increase of the factor. Multivariable survival models will also be used for estimating conditional HRs for the main clinical and epidemiological factors. Time-updated prognostic factors will be analyzed using extensions of the survival models aforementioned.

Despite all the efforts made for representativeness, the cohort might end up not being representative of the French general population of lymphoma patients. In that case, statistical techniques such as covariate adjustment methods [42] or methods based on the Inverse probability weighting (IPW) technique [43] could be implemented to correct for this bias [41, 44]. In that regard, the REALYSA setting in which the recruiting centers are located in *départements* also covered by PBCR will be very useful.

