#### Main prognostic epidemiological factors

For each topic, relevant indicators of exposure will be defined. As an example, the following topics will be analyzed to study their association with clinical outcomes (non-exhaustive list): tobacco smoking, alcohol consumption, socio-professional categories, medical history, medical family history of cancer, domestic exposures, occupational exposures. Additionally, for each analysis, potential confounding factors will be considered on a case-by-case basis, as they may influence the prognostic of lymphoma in the population, such as the international prognostic indexes, socio-economic status, lifestyle habits and treatments. Other potential confounding factors such as the population density, the presence of polluting industries, urban or rural status of the place of residence will be used whenever necessary. In case of a substantial amount of missing data in one or more potential confounders, we will rely on multiple imputation techniques.

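### The stated log-rank test and single-predictor Cox model make no allowance for correlation within centres, so p-values and intervals for centre- or area-linked factors will be too optimistic if outcomes differ between centres

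*Protocol article*

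**What the plan says.** The Generalities subsection of the Statistical analysis section names the method for a categorical baseline factor: a two-sided log-rank test, and a hazard ratio with 95% CI "as estimated from a Cox model including only this variable as predictor". A model with one predictor has no centre term, and no stratification of the test is mentioned. Continuous factors are cut at quantiles and handled the same way. Multivariable survival models are added for conditional hazard ratios, again without mention of centre.

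On the centres, the Recruiting centers section states "Thirty-five French hospitals/clinics are currently participating to the study", a mix of university hospitals, general hospitals, cancer centres and private facilities. The Abstract states "Patients are treated according to the standard practice in their center".

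The section on main prognostic epidemiological factors leaves confounders to be chosen case by case. Its candidates include treatments, prognostic indexes and socio-economic status, and also "the population density, the presence of polluting industries, urban or rural status of the place of residence". Centre is not on the list. The Representativeness analysis section compares confounders between centres twice a year, but as a check on recruitment and not as part of an outcome model.

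Nowhere does the article name centre strata, a centre frailty or a cluster-robust variance.

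**The concern.** The log-rank test and the usual Cox standard error treat patients as independent. That fails to protect the error rate when two things hold together: the outcome varies between centres, and the factor under study also varies between centres. If either is absent, the test keeps its level.

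The article makes both plausible for part of its programme. On the outcome side, care follows local practice in centres of very different type. On the factor side, the Abstract, the Background and the Discussion name the healthcare system as social institutional context, and environmental exposures, among the determinants of interest. The first of these is largely a property of the centre or area, and the second may be in part.

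For such a factor the effective sample size is closer to the number of centres than to the number of patients. Chance differences between a few centres could then be reported as a prognostic effect with a small p-value.

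**Working it through.** **Step 1. Reproduce the plan's figure.** Inputs from Sample size calculation: "with a 2-sided test at α = 0.05", "a power of 0.8 and an exposure prevalence of 10"%, and "We would need to observe 530 events to be able to detect a HR of 1.5". With the Schoenfeld formula:

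events = (1.960 + 0.842)² / [0.1 × 0.9 × (ln 1.5)²] = 7.849 / 0.014796 = 530.5

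The stated 530 reproduces, and 530/0.3 gives the stated 1767 patients with DLBCL. The formula assumes independent patients, so the planning figure contains no allowance for clustering.

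**Step 2. Design effect.** Take m = 1767/35 = 50.5 patients per centre (equal sizes assumed). Then

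- design effect = 1 + (m − 1) × ICC of exposure × ICC of outcome
- standard error multiplier = √(design effect)
- true two-sided error = 2 × P(Z > 1.96/√(design effect))

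The documents give neither ICC, so both are assumed over a range. Each cell shows the standard error multiplier and the true error.

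| Exposure ICC | Outcome ICC 0.01 | 0.02 | 0.05 |
|---|---|---|---|
| 0 | 1.00; 5.0% | 1.00; 5.0% | 1.00; 5.0% |
| 0.05 | 1.01; 5.3% | 1.02; 5.6% | 1.06; 6.5% |
| 0.20 | 1.05; 6.2% | 1.10; 7.3% | 1.22; 10.9% |
| 1 (constant within centre) | 1.22; 10.9% | 1.41; 16.5% | 1.86; 29.3% |

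Example: with exposure ICC 1 and outcome ICC 0.01, 1 + 49.5 × 0.01 = 1.495, √1.495 = 1.22, and 2 × P(Z > 1.60) = 10.9%.

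**Step 3. Simulation of the unstratified log-rank test under no effect.** The setting was 35 centres, 1767 patients, about 30% one-year events, 10% exposed, a normal centre effect on the log hazard and 2000 runs per scenario. The Monte Carlo standard error is about 0.5 points near 5% and 0.9 points near 19%.

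| Exposure | SD 0.1 | SD 0.2 | SD 0.3 |
|---|---|---|---|
| No clustering | 4.9% | 5.1% | 5.6% |
| ICC 0.2 | 5.3% | 6.6% | 7.7% |
| Constant within centre | 6.7% | 11.3% | 18.7% |

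**Step 4. Do the two approaches agree?** At 30% one-year events the cumulative hazard is −ln 0.7 = 0.357, so the event probability changes by 0.357 × 0.7 = 0.250 per unit of log hazard. The outcome ICC is then about (0.250 × SD)²/(0.3 × 0.7), that is 0.003, 0.012 and 0.027 for SD 0.1, 0.2 and 0.3. For a centre-constant factor the design effects are 1.15, 1.59 and 2.32, and the errors 6.7%, 12.0% and 19.8%. These are close to the simulated 6.7%, 11.3% and 18.7%. The outcome ICC of 0.05 in Step 2 therefore describes more variation between centres than any simulated case, and the simulated range is the one used for the conclusion.

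**The case against.** The strongest counter-case has four parts.

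- **The article names no variance estimator.** A single-predictor Cox model can carry a cluster-robust variance, and the handling of centre is often left to an analysis plan, which is not shown. This stands in part: the final analyses may allow for centre. But the article does fix a test, and an unstratified log-rank p-value makes no such allowance.
- **The subsection is headed as basic description.** That is true, yet it attaches a hypothesis test and a 95% CI to each factor, so their error rates matter.
- **Multivariable models with treatments and geography take up much of the centre effect.** They may reduce it. They do not give valid standard errors if variation between centres remains, and centre is not a listed covariate.
- **The example topics are mostly patient-level.** Smoking, alcohol, family history and occupational exposure vary within a centre, and residential history is lifelong. Centre is also not the same as area, since the two pilot départements have three to four centres each. This stands, and it limits the point: for such factors the inflation is nil to modest.

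A reader might infer three stronger points that the documents do not support:

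- **That intervals are too narrow for every exposure.** Without exposure clustering the simulated error stays at about 5%.
- **That centre practice confounds the univariable hazard ratio, as a defect of the plan.** That ratio is unadjusted by design, and adjusted models follow with treatments and geography as candidate confounders.
- **That every test and model must be stratified by centre.** Stratification changes the question to a within-centre contrast, loses information in small subtypes, and cannot estimate a factor that is constant within centre.

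**Conclusion.** The point holds for factors that vary mainly by centre or area, and only if outcomes also differ between centres. For a factor constant within centre, the true two-sided error at nominal 5% is about 7% to 19% for a centre log-hazard SD of 0.1 to 0.3. At an exposure ICC of 0.2 it is about 5% to 8%. With no exposure clustering it is about 5%.

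These figures rest on assumed centre variation, 35 centres of equal expected size, 1767 patients, 30% one-year events and 10% exposed. They show what could happen and do not estimate what will happen in this cohort. Other centre sizes, subtypes or prevalences would move them. The plan's 530 events is arithmetically correct under independence and is not in dispute.

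This is a cheap improvement to the stated analysis. It does not invalidate the cohort or its analyses of patient-level factors.

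**What to change.** Add a short paragraph to the analysis text:

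- **Factors linked to centre or area:** report Cox confidence intervals and p-values, univariable and multivariable, with cluster-robust variance by centre and a small-cluster correction, or from a model with a shared centre frailty. Use these in place of the plain log-rank p-value.
- **Individual-level factors:** keep the stated analysis and add the same approach as a sensitivity analysis only.

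The small-cluster correction should not be omitted. A centre-constant factor with 10% prevalence is carried by only three or four of 35 centres (0.1 × 35 = 3.5), and an uncorrected robust variance is unreliable with so few exposed clusters.

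The cost is analysis wording and code. Centre is already available, since the plan compares centres twice a year. The downside is somewhat wider intervals. For the centre-constant case these would be honestly wider: by a factor of 1.22 at an outcome ICC of 0.01, for example.

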#### Main prognostic epidemiological factors

For each topic, relevant indicators of exposure will be defined. As an example, the following topics will be analyzed to study their association with clinical outcomes (non-exhaustive list): tobacco smoking, alcohol consumption, socio-professional categories, medical history, medical family history of cancer, domestic exposures, occupational exposures. Additionally, for each analysis, potential confounding factors will be considered on a case-by-case basis, as they may influence the prognostic of lymphoma in the population, such as the international prognostic indexes, socio-economic status, lifestyle habits and treatments. Other potential confounding factors such as the population density, the presence of polluting industries, urban or rural status of the place of residence will be used whenever necessary. In case of a substantial amount of missing data in one or more potential confounders, we will rely on multiple imputation techniques.

### Ethics

The study is performed according to the declaration of Helsinki, and national laws and regulations for RIPH2 studies. The REALYSA study was approved by a French ethics committee (Comité de Protection des Personnes Ouest II - file number: 2018/46) and by the National Commission for data protection and freedom of information (CNIL - decision number: DR-2018-238). Written informed consent is obtained from patients before any data collection. A specific signed consent form is also obtained from each patient willing to participate in genetic studies that may be conducted on blood samples. Patients are free to refuse to participate or to withdraw from the study at any time. Collected data are anonymous and secure data management systems are used. Any substantial change of the protocol (e.g. number of centers, number of collected blood samples) will be validated by the ethics committee before implementation.

## Discussion

This cohort will include around 6000 patients with clinical, epidemiological and biological data. This initiative constitutes a great opportunity to set up and emulate collaborative research projects on a wide range of topics, with the overall aim of improving knowledge on lymphoma patients’ outcomes in real-life setting.

France is a particularly appropriate country to set up such study due to a global organization in diagnosis, clinical research and epidemiological surveillance of lymphoma patients. The LYSA is a very active and well-structured organization which brings together professionals specialized in the field of lymphoma across the country and plays a leading role in coordinating cutting-edge research projects on lymphoma. REALYSA also takes advantage of the presence of the national Lymphopath network to improve the quality of diagnosis of included patients [38]. As the LYSA is a group specialized in clinical trials in lymphoma, there is also a systematic diagnostic review for patients included in clinical trials by the hematopathologists of LYSA Pathology committee. For these reasons, we did not choose to centralize all tissue blocks as has been done in other lymphoma cohorts (e.g. LEO – SPORE [45]), but we created a virtual tumor bank for the accessibility of tumor tissues for specific studies. Finally, the close collaboration between REALYSA and FRANCIM offers an innovative opportunity for a formal evaluation of the representativeness of patients included in this prospective cohort by mapping data obtained from REALYSA inclusion and those recorded in registries. To the best of our knowledge, this type of prospective collaboration between clinical centers and registries is unique at a national level.

Other prospective cohorts are currently implemented such as the Haematological Malignancy Research Network (HMRN). In this population-based cohort, all hematological malignancies were prospectively included since 2004 in a specific geographical area of United Kingdom [46, 47]. The Lymphoma Specialized Program of Research Excellence (SPORE) Molecular Epidemiology Resource (MER) cohort enrolled prospectively patients from Mayo Clinic (Rochester, Minnesota) and the University of Iowa (Iowa City, Iowa) since 2002 [45]. Investigators extended this program in 2015 to eight US centers as part of the Lymphoma Epidemiology of Outcome (LEO) program (NCT02736357). The objectives of REALYSA cohort are close to the ones of these programs but we expect to have a cohort with as much as possible a national coverage with a control of the representativeness thanks to data from registries (see Fig. 2).

Although clinical trials remain the gold standard for the evaluation of new treatment options, a majority of lymphoma patients are currently treated outside clinical trials. In addition, large prospective phase III trials are now less frequent with the development of therapeutic trials targeting specific populations, for instance with a particular lymphoma pathogenesis. With comprehensive clinical/biological data collections, we will be able to determine the efficacy and toxicities of some treatment options performed in daily practice that avoid the problem of patient selection in clinical trials. For instance, we observed that the median age of DLBCL in general population is more than 70 years old [48], but was estimated near 60 years old in clinical trials or in clinic-based observational cohort from tertiary hospitals [49]. Comparison of patients with mantle cell lymphoma (MCL) included in clinical trials or registered in cancer registries showed that patients from clinical trials were younger and had less advanced stage; there was also an excessive mortality mainly in elderly MCL patients from registries confirming patient selection bias in clinical trials [50]. In this setting, we will also be able to prospectively validate clinical prognostic scores (e.g. FLIPI, MIPI) among real-life patients. The validation of clinical trial results in general population after approval is also a major challenge for new targeted therapies in lymphoma such as Chimeric Antigen Receptors (CAR) T-cells, new monoclonal antibodies or tyrosine kinase inhibitors regarding specificities of their uses, specific adverse effects and cost. For instance, in a recent study of the HMRN network, the impact of novel therapies in real-life settings for outcome of MCL patients was well documented [51]. In this context, a prospective cohort such as REALYSA will offer a better evaluation of new therapeutic options than retrospective studies with possibility of health-economic studies. For these new therapeutic options, a comparison between REALYSA patients included in clinical trials vs REALYSA patients not included in clinical trials will also be possible, as we collect information about clinical trial participation. The utility of RWD for the detection of rare or late toxicities is now well recognized [52]. For instance, after the publication of cardiac surveillance guidelines mostly based on RWD, the cardiac surveillance rate of lymphoma patients treated by anthracycline-based therapy seemed to improve [53]. The analysis of prospective RWD collections has informed clinical practice, in particular for rare lymphoma subtypes and for clinical situations for which designing clinical trials remains difficult: for instance, the modality of DLBCL and HL patient surveillance after first line therapy was modified by data coming from RWD showing the controversial use of routine CT-scan for the detection of relapses [54–56]; similarly, use of RWD contributed to the definition of new survival endpoints such as EFS24 in DLBCL or the comparison of patient life expectancy with general population [57–59].

Recently, there is a major effort to aggregate biological collections from several institutions or among consortium with samples coming from patients mostly treated in real-life setting. For instance, three major studies from a group of institutions investigated the relation between genome/exome sequencing with the prognosis of DLBCL patients [11, 60, 61]. In REALYSA, we will bank an important number of biological specimens, allowing ambitious biological and genetic studies to identify new biological markers from tumors but also from the host with germline DNA analyses. Interestingly, with the collection of clinical, biological and epidemiological data, we will be able to analyze the challenging question of the interaction between environmental exposure and tumor biology [62], as well as extend our previous works on the relation between inherent genetic variations analyzed by GWAS and prognosis [27].

The longitudinal evaluation of patients during follow-up is a major objective in our cohort. The collection of data regarding professional situation, reproductive health, health behaviors, appearance of new morbidities and evolution of QoL will be of great utility to describe and analyze specific challenges of daily living for lymphoma survivors in the general population. In this context, recent works in advanced-stage lung cancer showed that the self-reported symptoms during follow-up using a web-based application improved overall survival due to an early detection of relapse [63].

Several weaknesses may be identified in this study. First, unlike other cohorts (e.g. HMRN), not all lymphoid malignancies are included in REALYSA. We elect not to include patients with chronic lymphocytic leukemia (CLL)/lymphocytic lymphoma, primary central nervous system (CNS) lymphoma and post-transplanted lymphoma as there are other national networks for these lymphoid malignancies and their managements are very distinct from other NHL subtypes. Similarly, primary cutaneous T-cell lymphoma that are mainly diagnosed, treated and followed by dermatologists specialized in this disease are not included. Second, depending on the subtypes, the statistical power may be limited in some cases. Indeed, the comprehensive occupational and domestic exposure questionnaire, associated with clinical data, will help in understanding the role of environmental conditions (including socio-economic status, social institutional context, social relationships, environmental exposures, individual behaviors, lifestyle) on lymphoma prognosis. Previous studies suggested the potential prognostic impacts of some environmental exposures on lymphoma patient outcome [25, 62]. The major issue of these studies is to have sufficient statistical power to prove an association depending on exposure prevalence, the sample size of the lymphoma subtype and the number of events. We think that for the most frequent lymphoma subtypes, such as DLBCL, FL and HL, the power would be satisfactory to detect some environmental conditions as prognostic factors. We recognize that infrequent lymphoma subtypes or for low prevalence exposures, results will be considered as exploratory and will need further replications for instance through international collaborations.

Finally, there are three major challenges in this study. First, we will have to pay strong attention to recruitment dynamics and patient characteristics to avoid recruitment biases and to have a population as representative of the general population of lymphoma patients as possible. Strong guidelines are given to centers in order to recruit all patients meeting the inclusion criteria, without any distinction on age, general condition or clinical prognosis. Moreover, smaller and non-University centers were opened during the extension phase in order to capture a larger population of patients, including those treated outside University Hospitals. Interim analyses will be conducted in order to compare participants’ characteristics with registries data. Nevertheless, even if the cohort is not representative of the whole French population of lymphoma patients, we strongly believe that building such cohort will be of use for many research works despite the lack of representativeness, as long as the “scientific inference is still valid” [64, 65]. The second challenge is the retention of patients in the cohort. Prospective follow-up is tied to the diagnosis date, in order to follow clinical management (e.g. annual follow-up from diagnosis), thus facilitating patient engagement. Newsletters with information on the study and projects will be sent to patients, in order to create a sense of belonging to the study. A dedicated webpage has also been created and updated with information on study and projects. Lastly, we aim to involve patients as partners of this research in order to facilitate communication and feedbacks between the research team and the patients included in the cohort and eventually minimize the attrition rate. Finally, as for all real-world studies, data completeness remains a major challenge. However, this study being conducted by investigators and CRA belonging to the hematological departments, we trust that this will maximize our capacity to recover satisfactory data.

This cohort is a perfect framework for multidisciplinary projects, as well as national and international collaborations. The close partnership with the LEO study team [45] and InterLymph consortium [66] will facilitate international projects and comparative analysis. For some rare subtypes with low numbers (e.g. Burkitt lymphoma), data could be pooled with other international cohorts to obtain relevant and robust results for these rare lymphomas [67], as it was already and successfully performed in a large pooling initiative studying risk factors for 11 NHL subtypes on behalf of InterLymph consortium [68]. Proposals for collaborative research projects from all disciplines will be considered by the study team.

Trial status: recruiting.

Protocol version 2.0, date: 09-01-2020.

Start recruitment: 11-14-2018.

Approximate date recruitment completion: 11-14-2023.

